### 2.9. Study Variables

The primary outcome variables for the study of the impact of ttC on the maternal health continuum of care will be ANC utilisation, skilled birth attendance, and PNC. The ttC variable is nominally defined by whether the household received ttC or not as shown in the Table 2.

### 2.10. Data Analysis

After the data have been cleaned, they will be exported to STATA for analysis and Excel for better visualization. Descriptive and summary statistics will be drawn using the frequencies, measures of central tendency, and dispersion with proportions to provide a descriptive analysis of the context.

There will be cross tabulation of the chosen covariates (education level, birth parity, income, and age) with the intervention (ttC) to obtain their frequency distribution among the treatment and control arms together with the p-values. A logistic regression of the intervention and the covariates will be used to generate the propensity scores. A caliper width at the 20% of the standard deviation will be used for matching participants using the greedy nearest neighbor method in order to get the average treatment effects and the impact of the ttC intervention on the outcomes ANC, PoD, and PNC [40,41].

**
Sensitivity Analysis
**

Sensitivity analysis will be performed using the Rosenbaum bounds to test the conditional on the unobserved variables, and that the study is free from hidden bias [42]. This will use the rbounds commands in STATA version 14 ranging from 1 to 1.5 with an increment of 0.05. The gamma value will show whether hidden bias is present, as well as the robustness of the results to this potential hidden bias [43]. The sensitivity analysis results for the outcomes will demonstrate whether the treatment effects remain significant and robust to unobserved confounding, even in the presence of hidden bias. This should be across different gamma levels and confidence intervals to ensure the reliability and validity of treatment effects, therefore indicating stability [42,43].

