### Conceptual Framework

The conceptual framework for this study is based on an adapted Andersen’s Behavioural Model (shown in Figure 1). It shows how maternal health behaviours are influenced by ttC in the presence of various factors proposed by Andersen’s model [25,26]. According to Andersen’s model, predisposing, enabling, and need-based factors affect maternal healthcare utilization [27]. In the current study, predisposing factors include social and demographic factors such as the mother’s age, education level, parity, and marital status. The enabling factors include income level of the household and male involvement in the pregnancy journey. The need-based factors are the presence of chronic illnesses, and psychological issues of the mother. While of importance to the study is the impact of ttC on maternal health behaviours, Andersen’s model helps us to account for how predisposing factors, enabling factors, and need-based factors shape healthcare utilisation. Secondarily, it contributes to understanding the contextual factors influencing maternal health outcomes, which supports efforts to address healthcare access inequality and inform policy development for more equitable access to care [25,26]. 

In this study, we shall incorporate Andersen’s model in investigating the impact of ttC (as an intervention) on ANC utilisation, PoD, and PNC. The ttC is hypothesised to influence maternal healthcare utilisation across the above three aspects by improving mothers’ knowledge on the benefits of fast and sufficient ANC visits, thus improving their attitudes towards ANC. ttC is also hypothesized to improve male-involvement, as well as enhancing the mother’s awareness of their health status and history, thereby affecting PoD and creating need for PNC.

**
General Objective
**

The main objective of this study will be to assess the impact of ttC on the maternal health continuum of care outcomes in Northern Uganda.

**
Specific Objectives
**

To investigate the impact of ttC on ANC utilisation among pregnant mothers.To evaluate the impact of ttC on the advised place of delivery among pregnant women.To assess the impact of ttC on PNC utilisation among mothers.

**
Hypotheses
**

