## 2. Methods

### 2.1. Research Design

A cross-sectional quasi-experimental research design with retrospective data collection comparing the intervention group to the control group will be used. Because of the cross-sectional data collection, a randomised control trial is not an option and, therefore, propensity score matching will be used to improve causal inference in this experimental design, as has been used in other similar impact study settings [28,29,30]. PSM will match each treated unit with a nontreated unit of similar characteristics using propensity scores generated from chosen covariates. The preferred characteristics for matching so as to reduce bias and improve precision within the model in this study are education level, birth parity, income, and age of the participants [31]. 

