### 2.2. Research Area

The study area will be the northern region of Uganda, specifically the Oyam district, which was selected because ttC is implemented in the Aber subcounty of the district. Northern Uganda in particular is an important region for studying maternal health due to its high poverty rates [32], cultural diversity, limited healthcare access, poor health outcomes, and the presence of conflict-affected individuals [33].

Taking the Oyam district as the sampling frame, two subcounties, Aber and Otwal, are chosen for reaching out to mothers who would have given birth within the past 2–12 months. Aber is the treatment subcounty, and Otwal is the control subcounty because ttC is implemented in the former, but not in the latter. However, the two subcounties of Aber and Otwal were chosen because they are located within the same district and therefore have similar health challenges, such as limited health care access and similar poverty situations in the conflict-affected region [33]. Approximately 18.3% of the population in Aber and 22.3% of the population in Otwal aged 10–19 years have ever been married [34]. Furthermore, in 2021, these two subcounties, among others in Oyam district, had one of the highest teenage pregnancy rates in Uganda [35,36]. Factors mentioned by these new young mothers for the high rate of teenage pregnancy include a lack of knowledge of the ovulation period, inadequate sex education, and social norms that prevent parents from talking to their children about sex education [36]. Significantly, both subcounties are chosen because they do not share borders with each other; thus, limited spillovers are expected from the treatment subcounty to the control subcounty.

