11th visit at 18 months of life (PNC)	Giving three to four meals to the child a day, child sleeping under a mosquito bed net.

Note: CHW = community health worker, ANC = antenatal care, HIV = human immunodeficiency virus, AIDS = acquired immunodeficiency syndrome, STIs = sexually transmitted infections, PoD = advised place of delivery, PNC = early postnatal care, ttC = timed and targeted counselling.

**Table 2 mps-07-00098-t002:** Study variables and their definitions.

Variable	Definition of Variable	Answering Scale
Intervention Variable		
ttC	This is a behavioural change approach implemented through CHWs to pregnancy households with a wide range of life-saving health practices through appropriately timed messages delivered using interactive storytelling to improve maternal health service utilisation. Mothers will be asked whether they received ttC from a CHW during their pregnancy.	1 = Yes 0 = No
Outcome Variables		
ANC	This is defined as visits to skilled health personnel during pregnancy. Mothers will be asked whether they attended any ANC visits during pregnancy.	1 = Yes 0 = No
PoD	This refers to the advised place of delivery, in a health facility. Mothers will be asked where they gave birth, with answering options including private health facilities, government health facilities, traditional birth attendant’s homes, or their own homes.	1 = Yes 0 = No
PNC	This refers to the care given mothers immediately after birth. This includes at least one PNC visit within the first 6 weeks after delivery. Mothers will be asked whether they visited a health facility for PNC after delivery.	1 = Yes 0 = No
Independent Variables		
Predisposing Factors		
Age	Mothers will be asked for their age at their last birthday.	1 = <20 2 = 21–25 3 = 26–30 4 = 31–35 5 = 36–40 6 = >40
Education level	Mothers will be asked for the highest level of school ever attended.	1. Preschool 2. Primary 3. O Level 4. A level 5. Tertiary 6. University 7. Non
Parity	Mothers will be asked how many births they have had in their lifetime, including the most recent one.	
Marital status	Mothers will be asked for their current marital status.	1. Widowed 2. Married or living together 3. Divorced or separated 4. Never married or never living together
Enabling Factors		
Income level	This refers to the income of the household. Mothers will be asked, on average, what is their approximate maximum monthly.	1. <200,000 2. >200,000–<500,000 3. >500,000–<1,000,000 4. >1,000,000–<2,000,000

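### The propensity score leaves out marital status, which the protocol names as a driver of care use and collects, and two of its four covariates (age and income) are coded with gaps

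*Protocol article*

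**What the plan says.** **Covariates in the score.** Section 2.1 says the preferred matching characteristics "in this study are education level, birth parity, income, and age of the participants". Section 2.10 repeats the list in its "cross tabulation of the chosen covariates (education level, birth parity, income, and age) with the intervention (ttC" and then fits the logistic propensity model on those covariates. The two sections agree, so this is a stated choice and not a detail left open.

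**Drivers of care use.** The Conceptual Framework holds that predisposing, enabling and need-based factors affect use of maternal care. The predisposing factors include the mother's "age, education level, parity, and marital status". It adds: "The need-based factors are the presence of chronic illnesses, and psychological issues of the mother". Table 2 collects marital status and both need-based factors.

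**Answer scales.** Table 2 codes age as "1 = <20 2 = 21–25 3 = 26–30" and onwards in five-year classes to an open class above 40. It codes income as "1. <200,000 2. >200,000–<500,000 3. >500,000–<1,000,000", followed by a class strictly between 1,000,000 and 2,000,000.

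**Reliance on matching.** Strengths and Limitations presents matching as the substitute for randomisation that removes confounding bias. It lists only unmeasured confounders as a remaining problem and assigns those to the sensitivity analysis.

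**The concern.** Aber has ttC and Otwal does not, so any difference between the mothers of the two subcounties that also bears on care use can confound the comparison. Marital status is such a candidate by the protocol's own account. It is measured, so balancing it costs almost nothing, yet it is omitted and no reason is given. The Rosenbaum bounds in section 2.10 address unobserved variables and are no substitute for balancing one that is observed.

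The coding gaps affect variables that do enter the score. A mother whose true answer fits no class must be left blank, and so cannot be scored, or be put in a neighbouring class at the interviewer's discretion. Section 2.2 stresses young motherhood in these subcounties, so age 20 is not a remote case. Income is asked as an approximate amount, for which round figures are natural answers.

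**Working it through.** **1. Which named factors are in the score**

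| Factor in the framework | Collected in Table 2 | In the score |
|---|---|---|
| Age, education, parity | yes | yes |
| Marital status | yes, current status | no |
| Household income | yes | yes |
| Male involvement | yes, partner came to any ANC visit | no |
| Chronic illness | yes, current status | no |
| Psychological issues in pregnancy | yes | no |

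The four omissions are not alike.

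- *Male involvement* is rightly out. The framework states that "ttC is also hypothesized to improve male-involvement", and the item is accompaniment to ANC, so it must be 0 whenever ANC is 0.
- *Psychological issues during pregnancy* may arise after ttC has begun, so they too are rightly out.
- *Chronic illness* is asked as of the interview, 2 to 12 months after birth, and its examples include HIV/AIDS. Table 1 gives HIV testing as a focus of the second ttC visit, and the framework expects ttC to make mothers more aware of their health. As worded, a positive answer can be a result of ttC.
- *Marital status* is the clear omission, although it is also asked as current status.

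**2. The answer scales**

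Each age from 18 to 49 (the range sampled in section 2.8) was run through the printed codes. Only age 20 falls in no class. Of the incomes tried, 200,000, 500,000 and 1,000,000 have no class, because the inequalities are strict on both sides of each cut point. No class is shown for 2,000,000 and above.

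**3. The plan's own target, for scale**

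Inputs from section 2.7: proportions of 71.5% and 81.5%, mean 76.5%, z values 1.96 and 0.842, design effect 1.5, nonresponse 10%.

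- n = 2 × (1.96 + 0.842)² × 0.765 × 0.235 / 0.10² = 282.3
- 282.3 × 1.5 = 423.4, and 423.4 × 1.10 = 465.8, against 465 stated. The figure reproduces.
- Effective size per group after nonresponse and design effect: 465 × 0.9 / 1.5 = 279.

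**4. Illustration of bias (assumed inputs)**

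Bias in the risk difference ≈ (difference in prevalence left after matching) × (difference in outcome by that covariate).

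- 5 points × 5 points = 0.25 points, or 2.5% of the 10-point target
- 10 × 10 = 1 point, or 10%
- 10 × 20 = 2 points, or 20%
- 20 × 20 = 4 points, or 40%

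With no true effect, an outcome proportion of 71.5% and 279 per group, the standard error is √(2 × 0.715 × 0.285 / 279) = 0.038. The two-sided false-positive rate is then 5.0% at 0.25 points of bias, 5.8% at 1, 8.2% at 2 and 18.2% at 4.

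**5. Illustration of uncoded mothers (assumed shares)**

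- If 4% to 8% are aged 20: 0.04 × 930 = 37 to 0.08 × 930 = 74.
- If 10% to 30% name a cut-point income: 93 to 279 of 930.
- If 3% to 10% were actually lost from the score, power would fall from 79.7% at 279 per group to between 78.5% (270.6 per group) and 75.4% (251.1 per group).

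**The case against.** Several objections carry weight.

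- **The marriage figures.** Section 2.2 reports: "Approximately 18.3% of the population in Aber and 22.3% of the population in Otwal aged 10–19 years have ever been married". A reader might take the odds ratio, (0.223/0.777)/(0.183/0.817) = 1.28, or the 4-point gap as the imbalance in the study. The document does not support that. The figures describe ever-marriage at ages 10 to 19, whereas the sample is mothers of 18 to 49 and the item is current status. Matching on age, parity and education may also absorb part of any gap. The figures show only that marriage patterns may differ between the subcounties.
- **Matching as the only control.** A reader might infer this, but the Abstract promises adjusted odds ratios after matching. The adjustment set is unnamed. It could include marital status, but nothing says that it does.
- **Adding every collected factor.** It is tempting to ask for chronic illness as it stands. That would admit a variable ttC may change, for the same reason that male involvement is kept out.
- **Lost mothers.** Section 2.5 mentions numerical items, mandatory questions and a field pretest. Table 2 may therefore show reporting classes, and a boundary answer may simply go into an adjacent class. Loss from the score is possible but not established. The printed gaps still need closing.
- **Top income class.** Its absence may be an artefact of text extraction. The gaps at the three lower cut points do not depend on it.
- **Parity and balance checks.** Parity is already asked as a number of births. The p-values in section 2.10 belong to a cross tabulation described before the score is built, so they cannot be read as the balance test after matching. Neither is a fault here.

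**Conclusion.** The point holds for marital status and for the two answer scales. Sections 2.1 and 2.10 fix a score that omits a collected variable the protocol itself names as a driver of care use. The printed age scale has no code for 20, and the printed income scale has none at its own cut points.

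The consequence cannot be sized from the document. It gives no imbalance among the sampled mothers, no outcome gap by marital status, no share aged 20 and no income distribution. On the assumed ranges the bias runs from negligible (0.25 points) to material (4 points, two fifths of the planned effect), and the power loss is small. The change is recommended because it is cheap and the omission unexplained, not because a large bias has been shown.

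**What to change.** - Add marital status to the propensity model, with the question worded as of the start of the pregnancy, or state why it is left out.
- Add chronic illness only if the question is reworded to conditions known before the pregnancy. Otherwise leave it out.
- Keep male involvement and psychological issues during pregnancy out of both the score and the adjusted odds-ratio model, and name the covariates of that model.
- Record age in completed years.
- Make the income classes contiguous: below 200,000; 200,000 to below 500,000; 500,000 to below 1,000,000; 1,000,000 to below 2,000,000; 2,000,000 or more.

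The cost is a sentence or two in section 2.10 and small wording changes in the electronic questionnaire and its translation, made before it is fielded. The extra terms may lose a few matches within the caliper. The planned 465 per group is unaffected.

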### Strengths and Limitations

This study’s main limitation is the use of a cross-sectional dataset to experiment with an intervention. However, propensity score matching will be used as an alternative to a randomised trial by eliminating the bias due to confounding, and thereby ably applying causal inference for the results [30]. Another limitation would be the several unmeasured confounders which would improve precision if included in the study. This will be mitigated by using sensitivity analysis to sow robustness of the results to these unmeasured confounders [43]. There may be response bias due to self-reporting, which may affect the information gathered. This limitation will be addressed by providing confidentiality assurance to the study participants to allow them to answer more truthfully. Finally, spillover effects will be mitigated by having distant subcounties that do not share borders.

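### Section 2.10 says gamma shows whether hidden bias is present, but gamma is a bias the analyst assumes; and no bound for binary matched pairs is named

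*Protocol article*

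**What the plan says.** The protocol article, section 2.10, under Sensitivity Analysis, gives the Rosenbaum bounds two different purposes.

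- **Detection.** The bounds are to be used "to test the conditional on the unobserved variables, and that the study is free from hidden bias", and "The gamma value will show whether hidden bias is present, as well as the robustness of the results to this potential hidden bias".
- **Robustness.** The results "will demonstrate whether the treatment effects remain significant and robust to unobserved confounding, even in the presence of hidden bias". Strengths and Limitations takes the same line on unmeasured confounders: "This will be mitigated by using sensitivity analysis to sow robustness of the results to these unmeasured confounders".

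The procedure is fixed in one sentence: "This will use the rbounds commands in STATA version 14 ranging from 1 to 1.5 with an increment of 0.05". On reading the output: "This should be across different gamma levels and confidence intervals to ensure the reliability and validity of treatment effects".

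Table 2 codes antenatal care, place of delivery and postnatal care all as 1 = Yes, 0 = No. The antenatal item, for example, is "Mothers will be asked whether they attended any ANC visits during pregnancy". The abstract promises adjusted odds ratios with 95% confidence intervals after 1:1 matching. Section 2.10 does not say which statistic the named command computes.

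**The concern.** Gamma is the factor by which two mothers with the same matched covariates are allowed to differ in their odds of being in the treated group. The analyst chooses it. The data then say whether the finding survives that choice; they say nothing about which value is true. A result that is still significant at gamma 1.5 is compatible with large hidden bias, and one that fails at 1.1 is compatible with none.

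The misreading matters more here than in most studies. Treatment follows subcounty (Aber treated, Otwal control; section 2.2), and matching uses only education, parity, income and age (sections 2.1 and 2.10). The limitations section concedes several unmeasured confounders and names this analysis as the only mitigation. An analyst who follows the detection sentences could report that the study was tested and found free of hidden bias.

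A second, smaller question is whether the bounds suit the outcomes. With Yes/No outcomes each pair difference is −1, 0 or +1. A method designed for continuous differences may then give output of little use, and the plan names no binary version.

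**Working it through.** **1. Interpretation.** No arithmetic is needed. Section 2.10 sets gamma to 11 values from 1 to 1.5. A quantity fixed before the data are seen cannot be evidence from the data that bias is present or absent. The detection and robustness statements cannot both describe the same output, and only the robustness statement is correct.

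**2. Planning inputs (section 2.7).** Control 71.5%, intervention 81.5%, mean 76.5%, two-sided 5%, 80% power, design effect 1.5, nonresponse 10%. The stated formula gives

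2 × (1.96 + 0.842)² × 0.765 × 0.235 / 0.10² = 282.29; × 1.5 = 423.4; × 1.10 = 465.8.

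The plan states 465 per group. This agrees apart from rounding and is not in dispute.

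**3. Illustrative pairs.** Assumptions not in the document: 10% nonresponse leaves 465 × 0.90 ≈ 418 pairs, all are matched, and outcomes are independent within pairs.

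- Favouring ttC: 0.815 × 0.285 = 0.2323; × 418 ≈ 97 pairs
- Favouring control: 0.715 × 0.185 = 0.1323; × 418 ≈ 55 pairs
- Discordant: 152; tied: 266 (64%)

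**4. Binary bound.** The upper-bound one-sided p is P(Bin(152, Γ/(1+Γ)) ≥ 97):

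| Γ | 1.00 | 1.20 | 1.25 | 1.30 | 1.35 | 1.50 |
|---|---|---|---|---|---|---|
| p | 0.0004 | 0.0129 | 0.0239 | 0.0408 | 0.0652 | 0.1905 |

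The crossing is at about 1.25 for one-sided 0.025 and about 1.32 for one-sided 0.05.

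The critical gamma at 0.025 under other assumptions (exact binomial):

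| Pairs | Within-pair correlation | Critical Γ |
|---|---|---|
| 300 | 0 | 1.15 to 1.20 |
| 330 | 0 | about 1.19 |
| 465 | 0 | about 1.26 |
| 300 | 0.2 | 1.25 to 1.30 |
| 400 | 0.2 | 1.35 to 1.40 |
| 465 | 0.2 | 1.40 to 1.45 |

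All lie inside the planned grid.

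**5. If the named command is a signed-rank/Hodges-Lehmann routine.** This is an assumption; the document does not say so.

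*p-values.* Drop the zeros and let D be the number of discordant pairs, B the number favouring ttC and p = Γ/(1+Γ). All remaining differences have size 1 and share the rank (D+1)/2. That rank cancels, leaving z = (B − Dp)/√(Dp(1−p)), which is the McNemar bound. If the variance ignores ties, it is inflated by 2(2D+1)/(3(D+1)), about 4/3, so the bound is conservative. With 465 independent pairs (108 v 62 discordant):

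| Γ | 1.20 | 1.25 | 1.30 | 1.35 |
|---|---|---|---|---|
| Ties handled (= McNemar) | 0.0093 | 0.0182 | 0.0327 | 0.0544 |
| Ties ignored | 0.0207 | 0.0348 | 0.0550 | 0.0821 |

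The crossing moves by one grid step here, and by one to two steps over 300 to 465 pairs with correlation 0 or 0.2.

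*Estimates.* The Hodges-Lehmann estimate is the median of pairwise (Walsh) averages, which can only be −1, −0.5, 0, 0.5 or 1. With 418 pairs, 18.5% of the averages are negative, 46.6% are zero and 34.9% are positive. The median is therefore 0, although the risk difference is 0.10. It is also 0 with 330 and 465 pairs.

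**The case against.** The best defence is that the paragraph also states the proper purpose and the limitations section repeats it, so a competent analyst would read the output correctly. The mixed text is real and should be acknowledged. It does not cure the two false sentences, because the plan gives no reason to prefer one reading over the other.

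A reader might infer that the bounds will be wrong because the command is meant for continuous differences. The document does not support this. It does not say what the command computes, and even on the signed-rank assumption the p-value bounds equal McNemar's or are somewhat conservative under the usual handling of ties. Only the Hodges-Lehmann estimates and their intervals would be uninformative. Section 2.10 does mention confidence intervals but does not say of what kind, and the reported effect remains the odds ratio.

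A reader might also infer that stopping at 1.5 cuts off the answer. At the planned effect the critical value falls inside the grid in every case examined, so the ceiling could bind only for larger effects.

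Finally, that modest bias would overturn an on-target result is not itself a fault of the plan. It is what the planned grid would reveal if read correctly.

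**Conclusion.** The stated rule of inference is wrong, and this is certain from the text alone: the bounds can neither test for hidden bias nor show whether it is present. The passages in section 2.10 contradict each other on this, in the one analysis offered against unmeasured confounding.

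That no bound for binary pairs is named is a secondary weakness. Its effect depends on the assumption about the command: p-values right or slightly cautious, estimates and intervals uninformative.

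The critical gamma of about 1.25 (one-sided 0.025; about 1.32 at 0.05) shows how far a claim of no hidden bias would overstate the evidence. It rests on 418 matched pairs, independence within pairs and the facility-delivery rates. Antenatal and postnatal care will have other rates and were not examined. The correction should be made before analysis, and it leaves the design and sample size untouched.

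**What to change.** In section 2.10:

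1. Delete the two statements that the bounds test for freedom from hidden bias and that gamma shows its presence. State instead that gamma is an assumed degree of hidden bias and that the analysis does not test whether such bias exists.
2. Name a McNemar or Mantel-Haenszel type Rosenbaum bound for the three binary outcomes, to accompany the odds ratios.
3. Report for each outcome the critical gamma at one stated threshold. One-sided 0.025 matches the two-sided 5% level in section 2.7.
4. Keep the present grid, and extend it only for an outcome whose critical value is not reached by 1.5.

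The cost is a few sentences and possibly a different command, with no new data. The downside is that the robustness claim becomes more modest.
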